A flow chart for 2YL is presented in Figure 2. Twelve PHUs have been identified by local partners, and matched into pairs with corresponding delivery rates and distance to a referral hospital (Appendix 1). From these pairs, PHUs will be randomly allocated into intervention sites and control sites. With established approval from the Ministry of Health and Sanitation, health leaders at a district level will be approached by local research staff with an invitation for their PHUs to participate in the study. On the basis of local baseline data, we estimate that 36 women per PHU will participate, approximately 216 women per arm (Figure 1) (details of sample size calculations in page 23). In the event of changes to the PHUs serving a community during the study period (e.g. existing PHUs closing, new PHUs opening), we may invite a PHU to participate in the same randomised arm if it is serving the same community . Our rational is that this is a trial of a community-based intervention, we have allocated a treatment arm to the community, and the community are now accessing another facility. This approach will help us to maintain recruitment to both arms. For example, Yataya community has been randomised to the control arm. The new PHU that recently opened there will be automatically allocated to the control arm. We may also conduct a community based survey in those clusters with low numbers of pregnant adolescent girls to understand if numbers included in the trial are real or if there is overreporting of age in facilities.

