**Recruitment, consent, data collection** ≈**3-6 and** ≈**9-12 months**

Interviews, focus groups, photovoice

**(Routine data collection at 1year** (routine PHU visit)

**(Routine data collection at 1year** (routine PHU visit)

Figure 2. Two Young Lives pilot study flowchart

Randomisation

The unit of randomisation is the trial area (or cluster), rather than individual woman. The sixteen trial areas will be allocated cluster numbers. Randomisation will be managed via a secure web-based randomisation and data management system hosted by MedSciNet with telephone back-up available at all times. Randomisation to intervention sites (2YL) and control sites (usual care) will occur in a 1:1 ratio. A minimisation algorithm will be used to ensure balance between the groups with respect to PHU use and distance to referral hospital. MedSciNet will write the randomisation program and hold the allocation code.

Intervention: 2YL mentoring scheme + usual maternity care

Women in the intervention group will receive the 2YL mentoring scheme provided as an adjunct to usual maternity care. Using the TIDieR reporting guidance^11^, a description of the intervention is as follows:

*Brief name*. 2 Young Lives mentoring scheme for pregnant teenagers and young mothers in Sierra Leone.

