# Data analysis

# Sample size calculation

Sample size estimation has been provided by the trial statistician, [name], co-investigator and Reader in Medical Statistics, KCL. Based on experience with some of the proposed trial areas and global maternal health literature relevant to these settings^3,6^, we estimate the risk to adolescent pregnant women in Sierra Leone of experiencing a primary outcome (one of maternal death or stillbirth or neonatal death with no double counting) to be approximately 20% of all adolescent women. We also estimate a modest intra-cluster correlation of 0.02 (sites similar but not identical, and a simple exchangeable autocorrelation structure based on previous experience in Sierra Leone)^6^.

Prior to full proposal development, the 2YL team visited a typical peri-urban PHU similar in size and distance to referral hospital to trial sites. At least 16% of all deliveries among teens resulted in maternal death, stillbirth or early neonatal death. It was not possible to include late neonatal deaths up to 28 days. In addition, girls who were referred to a referral hospital in an emergency were not included in these numbers. We believe that this data can match the indicative estimate of 20% of girls experiencing a primary outcome.

This study is planned as a pilot, with main stated aim to demonstrate the feasibility of a fully powered study, and to help with its design. But for the purpose of the power calculation (intention to treat and not per protocol), an assumption of at least 42 deliveries per site has been made, with 20% having primary outcome composite events during the trial duration.  These numbers will provide 84% power to detect a 52% relative risk reduction (RRR) of the primary outcome (from 20% to 9%) assuming a models ICC 0.02.

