We will pilot the use of photovoice as a participatory research methodology using small group discussions of photographs with young women. Photovoice is a photographic technique developed by Wang and Burrithat^20^ that puts cameras into the community members’ hands to help them to record, reflect upon, critically dialogue and share knowledge about their perspectives and priorities to reach policy makers^20,21^. These are all central elements of empowerment, a concept that is intertwined with the photovoice approach from its original conceptual underpinnings to its implementation^22^. While photovoice aims to foster social change, it can also enhance community engagement, increase awareness of community resources, and improve collaboration with research partners to help reduce health inequalities^23,20^ Photovoice has previously been used in vulnerable communites in Sierra Leone^24^ and other settings^-25-28^ Thus, this approach offers a unique opportunity and gain understanding about the social and cultural factors that may facilitate potential scale up and sustainability of the 2YL mentoring scheme in young women, that other research methods such as surveys and interviews may not fully capture.

Feasibility of health economics

It would not be appopiate to conduct a full economic evaluation for a pilot study designed to estimate the parameters needed to design a future definitive trial - should not provide estimates of treatment effectiveness because the samples often have no or limited power to reliably detect between group differences. Thus, the focus of health economics in this pilot trial will be limited to developing or refining service use schedules and other measures of outcomes (i.e. piloting of a metric for risk-benefit assessment previously used in LMICs).

We will explore the resource use associated with the mentoring scheme and savings or other service use impacts (e.g. examining clinical records, based on clinical opinions) and will also estimate costs associated with the delivery of the scheme (components will include, e.g. recruitment and training of mentors, stipends, bursaries for girls, social gatherings). Cost consequences analyses will be used to present the results from this pilot study, as the costs and effects observed can also be used in value of information modelling to determine whether the cost of a definitive RCT is worthwhile.

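### The 84% power figure names no test level and no number of clusters: with the 12 clusters planned it is about 70–75% at two-sided 5%, and the 52% reduction does not match 20% to 9%

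*Protocol*

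**What the plan says.** Under Sample size calculation, the Protocol assumes an ICC of 0.02 and a 20% risk of the composite of maternal death, stillbirth or neonatal death. For cluster size, "an assumption of at least 42 deliveries per site has been made", "with 20% having primary outcome composite events during the trial duration". The conclusion is: "These numbers will provide 84% power to detect a 52% relative risk reduction (RRR) of the primary outcome (from 20% to 9"%. No alpha, sidedness or number of clusters is given there.

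Other sections supply or contradict the missing inputs:

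- Study design, setting and population lists 12 areas, and the flowchart (Figure 2) shows six clusters per arm.
- Clusters and participant selection and enrolment, which refers the reader to the sample size calculation, says "we estimate that 36 women per PHU will participate, approximately 216 women per arm".
- Randomisation says "The sixteen trial areas will be allocated cluster numbers", and the intervention description speaks of teacher training in eight intervention sites.
- Appendix 1 lists 12 sites with 2020 births to mothers under 19. The inclusion criterion is age under 18.

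**The concern.** A power statement can be checked only if the test level, the number of clusters, the cluster size and the two risks are fixed. Here the first two are absent from the sentence, the third has two values, and the two risks disagree with the relative reduction printed beside them. A reader who fills the gaps in the usual way (two-sided 5%, 12 clusters) does not get 84%.

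Two things are at stake. A null clinical result would be read against an implied 16% chance of missing the planned effect, when under that usual reading it is about 25–30%. In addition, the sample size calculation is itself a listed feasibility outcome, and the pilot is meant to inform a definitive trial, so an unclear figure would be carried forward.

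**Working it through.** **Inputs.** Control risk p1 = 0.20, intervention risk p2 = 0.09, ICC = 0.02, m = 42 (all from Sample size calculation); m = 36 (enrolment section); k = 6 clusters per arm (Figure 2). Alpha is not stated, so both two-sided 5% and one-sided 5% are assumed in turn.

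**Formulas.** Design effect DE = 1 + (m − 1) × ICC. Effective number per arm n = k × m / DE. Unpooled SE = √[(p1(1 − p1) + p2(1 − p2)) / n]. Power = Φ((p1 − p2)/SE − z), with z = 1.960 (two-sided) or 1.645 (one-sided). The pooled version uses the pooled SE for the critical value and gives slightly lower figures. Both are shown below.

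**Trying to reproduce 84%, 12 clusters of 42.**

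- DE = 1 + 41 × 0.02 = 1.82; n = 252/1.82 = 138.5.
- SE = √[(0.1600 + 0.0819)/138.5] = 0.0418; 0.11/0.0418 = 2.63.
- Two-sided 5%: Φ(2.63 − 1.96) = 74.9% (pooled 74.1%). Not reproduced.
- One-sided 5%: Φ(2.63 − 1.645) = 83.8% (pooled 83.3%). Reproduced, but under a test the Protocol does not declare.

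**Trying sixteen clusters (k = 8), two-sided 5%.**

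- m = 42: n = 336/1.82 = 184.6; power 86.0% (pooled 85.4%).
- m = 36: DE = 1.70, n = 288/1.70 = 169.4; power 82.9% (pooled 82.3%).

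These values lie either side of 84%.

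**With the 36 per health unit of the enrolment section, 12 clusters.** DE = 1.70; n = 216/1.70 = 127.1; 0.11/0.0436 = 2.52. Power is 71.3% two-sided (pooled 70.4%) and 81.0% one-sided (pooled 80.4%).

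**The relative reduction.** 1 − 0.09/0.20 = 0.55, not 0.52. A 52% reduction gives 0.20 × 0.48 = 0.096. With 12 clusters of 42 and p2 = 0.096, power is 69.3% two-sided (pooled 68.5%) and 79.3% one-sided (pooled 78.8%).

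| Clusters × size | Risks | Two-sided 5% | One-sided 5% |
|---|---|---|---|
| 12 × 42 | 20% v 9% | 74–75% | 83–84% |
| 12 × 36 | 20% v 9% | 70–71% | 80–81% |
| 12 × 42 | 20% v 9.6% | 69% | 79% |
| 16 × 42 | 20% v 9% | 85–86% | not needed |
| 16 × 36 | 20% v 9% | 82–83% | not needed |

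**Small-sample caution.** Twelve clusters in two arms leave 12 − 2 = 10 degrees of freedom. Referring the same ratios (2.63 and 2.52) to a noncentral t with 10 df at two-sided 5% gives about 66% at 42 per site and 62% at 36.

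**Where 42 may come from.** The Appendix 1 births to mothers under 19 sum to 504, and 504/12 = 42.0. That points to the 12-site list. Against this, its site numbers run to 8a and 8b with 1a, 3a, 6a and 7b absent, which suggests an eight-pair layout. The origin of the 84% cannot be settled from the Protocol.

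**The case against.** The best reply is that the Protocol never claims a two-sided test, and 12 clusters of 42 at one-sided 5% do give 83–84%. That stands. A reader might infer that the 12-cluster design flatly fails to deliver its stated power, and the text does not support so strong a statement: the shortfall is conditional on two-sided 5%. The one-sided reading still needs 42 rather than 36 per site and 9% rather than the stated 52% reduction.

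It is also fair to say that the study is a pilot whose declared aim is feasibility, and that no decision hangs on the 84%. That limits the weight of the point but does not make the figures consistent.

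Four further inferences are tempting but not supported:

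- *That 62–66% is the true power.* The Proposed analysis section specifies logistic regression with cluster-adjusted standard errors and no degrees-of-freedom correction. Such a correction is commonly left to the analysis plan, so the 10-df figures are a caution and not an error in the 84%.
- *That 42 cannot be a minimum because it is the Appendix 1 mean.* Appendix 1 covers one year, and the trial period is 24 months. The smallest sites, at 28 births a year, would give 28 × 2 = 56 before restricting to under 18, and the yield after that restriction is not given.
- *That capped mentor places dilute the intention-to-treat effect.* The cap is written as 36 per month per cluster, well above the monthly births in Appendix 1. Nothing says that the 9% presumes full uptake.
- *That the Protocol itself concedes low power for the clinical outcome.* The remark that "samples often have no or limited power to reliably detect between group differences" explains why no full economic evaluation is planned. It does not classify the clinical comparison.

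**Conclusion.** The point holds in conditional form. The power sentence omits alpha, sidedness and the number of clusters. With the current 12 clusters, ICC 0.02 and 20% v 9%, two-sided 5% gives about 74–75% at 42 per site and 70–71% at 36 (normal approximation). The chance of missing the planned effect is then about 25–30%, against the 16% implied. The 84% depends on an undeclared one-sided 5% test at 42 per site, or roughly on sixteen clusters that the design no longer has.

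Two defects need no assumption about alpha: 20% to 9% is a 55% reduction and not 52%, and the expected cluster size is 42 in one section and 36 in another. The conflict between 12 and sixteen areas is likewise plain on the page. The Protocol does not settle which cluster size is the intended denominator, so no single replacement power can be imposed. The correction should be made, but the feasibility aims do not depend on it.

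**What to change.** In Sample size calculation:

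1. State alpha, sidedness and 12 clusters (six per arm) in the power sentence.
2. Make the effect consistent: either 20% to 9% as a 55% reduction, or a 52% reduction as 20% to 9.6%.
3. Reconcile 42 with 36 per site. Say whether the figure is per year or over the whole trial, and note that Appendix 1 counts mothers under 19 while eligibility is under 18.
4. Correct the sixteen areas under Randomisation and the eight intervention sites in the intervention description so that they agree with the 12-cluster design.
5. Restate the power on the reconciled inputs. At two-sided 5% with 20% v 9% (normal approximation) this is about 75% at 42 per site or 71% at 36. Add that a 10-df reference would lower it to about 66% or 62%.

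The cost is wording only, with no extra participants. The stated power becomes less favourable.

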# Proposed analysis

We will undertake two statistical analyses: one pragmatic, intention to treat analysis (ITT) to compare intervention and control clusters that include all adolescent girls as originally allocated after randomization; and a complementary per protocol (PP) analysis to compare intervention and control clusters that includes only those girls who completed the intervention originally allocated. The CONSORT guidelines for reporting of parallel group RCTs recommend that both ITT and PP analyses should be reported for all planned outcomes to allow readers to interpret the effect of an intervention. It is not possible to blind clusters to interventions they receive, but outcome assessments will be blinded.

The main analysis will be pragmatic and by logistic regression adjusting the standard errors for clustering. This gives equal weight to each woman. A secondary analysis using random effects generalised least squares (GLS-RE) will also be attempted, although past experience is that the model might not converge to give any useable results. We will adjust for important baseline differences that might be related to outcomes (e.g. parity, gestation at first antenatal visits). As individual-specific data will be used there is a potential for missing data; but the main impact of missing data would be to invalidate the randomised comparison if there was unequal dropout between the two arms, leading to potential boas. Multiple regression, as described, would correct for any such bias.

Qualitative data from interviews with women and focus groups discussions with mentors, healthcare providers and stakeholders with be analysed using Braun and Clarke's six-phase approach to thematic analysis^18^. In brief, this includes familiarisation with the data, generation of initial codes, the searching for and review of themes, naming and offering explanations for each theme, and lastly producing a report. This practical analytic approach involves inductive coding practices which are both consultative and initially open^19^, and thus helpful to explore the perspectives of different research participants, highlighting similarities and differences, and generating unanticipated insights^18^.

We will pilot the use of photovoice as a participatory research methodology using small group discussions of photographs with young women. Photovoice is a photographic technique developed by Wang and Burrithat^20^ that puts cameras into the community members’ hands to help them to record, reflect upon, critically dialogue and share knowledge about their perspectives and priorities to reach policy makers^20,21^. These are all central elements of empowerment, a concept that is intertwined with the photovoice approach from its original conceptual underpinnings to its implementation^22^. While photovoice aims to foster social change, it can also enhance community engagement, increase awareness of community resources, and improve collaboration with research partners to help reduce health inequalities^23,20^ Photovoice has previously been used in vulnerable communites in Sierra Leone^24^ and other settings^-25-28^ Thus, this approach offers a unique opportunity and gain understanding about the social and cultural factors that may facilitate potential scale up and sustainability of the 2YL mentoring scheme in young women, that other research methods such as surveys and interviews may not fully capture.

Feasibility of health economics

It would not be appopiate to conduct a full economic evaluation for a pilot study designed to estimate the parameters needed to design a future definitive trial - should not provide estimates of treatment effectiveness because the samples often have no or limited power to reliably detect between group differences. Thus, the focus of health economics in this pilot trial will be limited to developing or refining service use schedules and other measures of outcomes (i.e. piloting of a metric for risk-benefit assessment previously used in LMICs).

We will explore the resource use associated with the mentoring scheme and savings or other service use impacts (e.g. examining clinical records, based on clinical opinions) and will also estimate costs associated with the delivery of the scheme (components will include, e.g. recruitment and training of mentors, stipends, bursaries for girls, social gatherings). Cost consequences analyses will be used to present the results from this pilot study, as the costs and effects observed can also be used in value of information modelling to determine whether the cost of a definitive RCT is worthwhile.

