# Methods

# Study design, setting and population

The design is a pilot cluster randomised controlled trial (cRCT) of the introduction of the 2YL mentoring adjunct to maternity care in Sierra Leone. The RCT will run in the communities served by the following 12 areas, representing a range of urban and rural settings:

| 1. Tombo town CHC | 7. Moriba Town (Lower Banta) CHP |
| --- | --- |
| 2. Mattru Town CHC | 8. Madina (Bum) CHC |
| 3. PAYCY's Clinic | 9. Senehun (Kamajei) CHC |
| 4. Taiama (Kori) CHC | 10. Moyamba Junction CHC |
| 5. Lengekoro CHP | 11. Heremakono MCHP |
| 6. Calaba Town CHC | 12. Yataia CHP |

The Standard Protocol Items Recommendations for Interventional Trials (SPIRIT) Figure adapted for the 2YL trial is shown below in Figure 1:

|  |  | **STUDY PERIOD** | | | | | | | | | | |  |  |
| --- | --- | --- | --- | --- | --- | --- | --- | --- | --- | --- | --- | --- | --- | --- |
|  | **Randomi-sation** | **Post-allocation** | | | | | | | | | | |  | **Close out** |
| **Timepoint*** | ***t_0_*** | ***t_1_*** | ***t_2_*** | ***t_3_*** | ***t_4_*** | ***t_5_*** | ***t_6_*** | ***t_7_*** | ***t_8_*** | ***t_9_*** | ***t_10_*** | ***t_11_*** | ***t_12_*** |  |
| Allocation | X |  |  |  |  |  |  |  |  |  |  |  |  |  |
| **Intervention** |  |  |  |  |  |  |  |  |  |  |  |  |  |  |
| *[2YLs+ usual care]* |  |  |  |  |  |  |  |  |  |  |  |  |  |  |
| *[Usual Care]* |  |  |  |  |  |  |  |  |  |  |  |  |  |  |
| **Assess-ments:** |  |  |  |  |  |  |  |  |  |  |  |  |  |  |
| *Composite primary outcome* |  | X | X | X | X | X | X | X | X | X | X | X | X |  |
| *Secondary outcomes* |  | X | X | X | X | X | X | X | X | X | X | X | X |  |

****_0_***, ***t_1-12_*** = Two months-time period

Figure 1. SPIRIT figure adapted for the 2YL trial

Sierra Leone is classified as a low-income country and has one of the highest mortality rates in the word, with a high burden of communicable and non-communicable diseases. It struggles to provide basic universal health coverage (UHC) and potable water and sanitation. Sexual violence and rape are common, and capacity to provide treatment to affected women and girls is extremely limited (State of Emergency over rape and sexual violence was declared in 2019). Sierra Leone also suffers an inadequacy of human resources for health; it has 2 skilled providers (doctors, nurses and midwives) per 10,000 population which is well below WHO’s health workforce targets for UHC and Sustainable Development Goal of 23.

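### The main analysis uses cluster-adjusted standard errors on 12 clusters without a small-sample correction; run in its usual form, it gives intervals that are too narrow and a false-positive rate of about 9 to 11%

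*Protocol*

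**What the plan says.** The protocol's section on study design, setting and population fixes the number of clusters: "The RCT will run in the communities served by the following 12 areas". The study flowchart shows six in each arm, and the Randomisation text confirms equal allocation: "Randomisation to intervention sites (2YL) and control sites (usual care) will occur in a 1:1 ratio". That same text still carries a different count, "The sixteen trial areas will be allocated cluster numbers", which conflicts with the 12 listed sites.

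Under Proposed analysis the main comparison is set out as "The main analysis will be pragmatic and by logistic regression adjusting the standard errors for clustering", with every woman weighted equally. The secondary analysis is described as follows: "A secondary analysis using random effects generalised least squares (GLS-RE) will also be attempted, although past experience is that the model might not converge". Adjustment for baseline differences is planned, with parity and gestation at first antenatal visit as examples. The section names no small-sample correction, reference distribution, degrees of freedom, cluster-level test or permutation test.

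The sample size section plans on a control risk of "to be approximately 20% of all adolescent women", an ICC of 0.02, and 84% power for 20% versus 9%; on cluster size, "an assumption of at least 42 deliveries per site has been made". The enrolment text gives another size: "we estimate that 36 women per PHU will participate, approximately 216 women per arm".

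**The concern.** The sandwich variance is a large-sample method in the number of clusters, not the number of women. With six clusters per arm, each arm's variance rests on six cluster residuals around an estimated mean. It is therefore biased downwards and is itself variable. Referring the result to a normal distribution ignores that variability, so the two errors add.

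The protocol powers this comparison and promises to report the effect on the composite and its components. Potential treatment effects are among the things the study aim says will be assessed, and the health economics section says observed costs and effects can inform modelling of whether a definitive trial is worthwhile. Intervals for the composite and other binary outcomes that are too narrow would understate uncertainty, which a pilot in particular needs to convey.

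**Working it through.** **Inputs.** From the protocol: 12 clusters, 6 per arm; 42 women per cluster (sample size section) or 36 (enrolment text), or the Appendix 1 counts of births to under-19s (28 to 65); risk 20%; ICC 0.02. Assumed, because not stated: two-sided 5%, ordinary sandwich, normal reference.

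**The plan's own figure first.** The design effect is 1 + (42 − 1) × 0.02 = 1.82. Effective n per arm is 6 × 42 / 1.82 = 138.5. A two-sided 5% test of 20% versus 9% then has 74.1% power, not the stated 84%. With 16 clusters, effective n is 8 × 42 / 1.82 = 184.6 and power is 85.4%, so the stated figure looks closer to a 16-cluster design. This gap arises before any small-sample issue and is a separate sample-size matter.

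**Analytic check of the false-positive rate (equal clusters).** With k = 6 per arm, the uncorrected sandwich has expectation (k − 1)/k = 5/6 of the true variance. With the common factor G/(G − 1) = 12/11, the ratio is 5/6 × 12/11 = 0.909. The statistic behaves approximately as a t(10) variable divided by the square root of this ratio, so the effective cut-off is the nominal one times that root.

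| Variance | Reference | Effective cut-off | P(abs t(10) > cut-off) |
|---|---|---|---|
| Uncorrected | normal | 1.96 × 0.913 = 1.789 | 10.4% |
| × 12/11 | normal | 1.96 × 0.953 = 1.869 | 9.1% |
| Uncorrected | t(10) | 2.228 × 0.913 = 2.034 | 6.9% |
| × 12/11 | t(10) | 2.228 × 0.953 = 2.124 | 6.0% |
| × 6/5 (that is, k/(k − 1)) | t(10) | 2.228 | 5.0% |

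**Simulation (beta-binomial, 20% in both arms, ICC 0.02, 200,000 trials per scenario, normal reference unless stated).**

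| Cluster sizes | Uncorrected | × 12/11 | × 6/5 with t(10) | Cluster-level t-test |
|---|---|---|---|---|
| 12 × 42 | 10.3% | 9.0% | 4.8% | 4.9 to 5.0% |
| Appendix 1 | 11.0% | 9.7% | 5.3% | 4.9 to 5.0% |

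Clusters of 36 give 10.3% and 9.0% in the first two columns. The mean estimated standard error is 0.88 (uncorrected) or 0.92 (× 12/11) of the true standard deviation, that is 12% or 8% too small.

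**Sensitivity.**
- Risks of 9 to 20% and ICC 0 to 0.05: 8.5 to 10.6% with the 12/11 factor and 9.8 to 12.0% without.
- Two individual-level covariates: 8.9 to 9.9% with the factor and 10.3 to 11.4% without.
- Pairing that explains 25%, 50% or 75% of the between-cluster variation: 7.6%, 6.0% or 4.6% with the factor, and 8.7%, 7.0% or 5.4% without.
- 16 clusters of 42: 7.9% with the factor and 8.8% without. The problem is smaller there but still present.

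**Power for 20% versus 9%, 12 × 42, simulated.** Normal reference with the 12/11 factor: about 77%. Corrected sandwich with t(10): about 65%. Cluster-level t-test: about 67%.

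**The case against.** The strongest reply is that the conditions behind the 9 to 11% are supplied by the reader. The protocol says only that standard errors are adjusted for clustering. It gives no sandwich type, reference distribution or significance level, and such detail is often left to an analysis plan, which was not available here. A corrected sandwich with t(10) would fit the existing wording. This stands as a reason for conditional wording. It does not remove the point, because the named method in its ordinary form does not hold its level at 12 clusters and nothing in the text guards against that form.

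It also stands that the normal reference accounts for most of the excess. With the 12/11 factor, changing only the reference to t(10) lowers the rate from 9.1% to 6.0%. Balanced allocation could lower it too. The protocol speaks of matched pairs in one place and minimisation in another, and gives no figure for the variation either would explain, so a range is all that can be given.

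Four stronger readings are tempting and not supported.
- A reader might infer that the intervals drive a go/no-go decision. No such rule is stated, and the primary objective is feasibility.
- A reader might infer that the main analysis is left without a valid fallback. The random-effects model is called a secondary analysis, and the convergence warning concerns that model only.
- A reader might extend the error rate to every secondary outcome. Several, such as birthweight and visit counts, are not binary, and only a binary composite was examined.
- A reader might see a contradiction between planning in relative risk reduction and fitting a logistic model. The protocol fixes no effect measure, and a risk ratio can be derived from that model.

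**Conclusion.** The point holds in conditional form. At 12 clusters, 20% risk and ICC 0.02, the stated analysis run with an ordinary sandwich, a normal reference and a two-sided 5% level has standard errors about 8 to 12% too small and a false-positive rate of about 9 to 11%. The rate is about 6% with t(10) alone (with the 12/11 factor), and about 5 to 8% if the allocation scheme absorbs 25 to 75% of the between-cluster variation. The consequence is overstated precision for the composite and other binary outcomes. It is moderated because this is a feasibility pilot, but the protocol does power and promise the comparison. The whole distance from 84% to about 65 to 67% power should not be attributed to this choice, since part of it is the separate sample-size mismatch.

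**What to change.** Amend Proposed analysis to name a method valid for 12 clusters. There are two suitable options:

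- a cluster-level analysis: a t-test on cluster proportions, or a two-stage covariate-adjusted version, on 10 degrees of freedom less any cluster-level covariates; or
- the logistic model with a small-sample-corrected sandwich (for example Kauermann-Carroll or Fay-Graubard) and a t(10) reference.

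State the significance level and sidedness. If the logistic model stays as the main analysis, name the cluster-level analysis as the secondary one in place of GLS-RE; it does not depend on convergence. Say whether allocation was paired or minimised: if pairing does absorb variation, an unpaired corrected test becomes conservative (3.9%, 2.9% or 2.2% in the 25%, 50% and 75% scenarios). Reporting a risk ratio beside the odds ratio is optional.

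The change costs a few sentences and lines of code. The price is wider intervals and lower power, about 65 to 67% for 20% versus 9% at 12 × 42.
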